### 3.2. Metabolic Parameters

With regard to the blood tests carried out, 237 participants consented to their extraction: 109 in the intervention group and 128 in the control group. There were slight significant differences in glucose, total cholesterol, and LDL cholesterol levels. Blood tests detected 21 cases of impaired fasting blood glucose and 24 cases of hypercholesterolemia. Table 4 summarizes the results.

**TABLE 4 tbl-0004:** Pre‐intervention analytical characteristics.

	Control (*N* = 109)				Intervention (*N* = 128)				*p*‐values
	Mean (%)	SD	Min.	Max.	Mean (%)	SD	Min.	Max.	
Glucose^∗^ (mg/dL)	90.1	6.9	72	114	93.1	6.9	77	114	0.0023^†^ ^∗^
Triglycerides (mg/dL)	62	28	26	211	57.6	25.4	29	251	0.2156
Total cholesterol^∗^ (mg/dL)	164.5	28.8	103	242	173.7	27.8	109	295	0.0266^†^ ^∗^
LDL cholesterol ^∗^ (mg/dL)	88.1	22	32	143.3	98.2	23.9	54.8	210.5	0.0026^†^ ^∗^
HDL cholesterol (mg/dL)	64	13.1	38.7	96.7	64	11.1	44.1	91.4	0.9782
Urea (mg/dL)	26.4	5.7	16	45	27.7	5.2	17	41	0.0642
GOT (AST) (UI/L)	32.6	7.1	19.2	68.9	33.7	6.5	21.4	58.4	0.1778
GPT (ALT) (UI/L)	18.9	8	9.3	68.4	18.7	5.2	9.7	38	0.7845
Hemoglobin (g/dL)	13.3	0.8	10.3	15.5	13.4	0.7	11.6	15.9	0.1424
Creatinine (mg/dL)	0.5	0.07	0.3	0.6	0.5	0.06	0.3	0.6	0.6317
CRP (mg/dL)	0.1	0.2	0.02	1	0.1	0.2	0.02	1	0.5331
Insulin (μUI/mL)	5.7	4.6	0.7	32.5	6.7	7.6	1.2	53.9	0.2915
HOMA index	1.3	1.2	0.1	8.7	1.6	1.9	0.2	15.2	0.1665^†^

*Note:* Min, minimum; Max, maximum.

Abbreviations: CRP, C‐reactive protein; HDL, high density lipoprotein; LDL, low density lipoprotein; SD, standard deviation.

^†^Kruskal–Wallis.

^∗^
*p*‐value < 0.05.

### 3.3. Physical Activity

Daily moderate/vigorous activity was, on average, 4.2 ± 1.2 h (252 ± 72 min), with significant differences between school and nonschool days (*p* < 0.001) (Figure 2(a)), and between morning (8:30–16 h) and afternoon (16:00 to 21:00 h) intervals (*p* < 0.001) (Figure 2(b)). We found statistically significant differences in moderate/vigorous activity during the school day mornings and afternoons among center types (*p* < 0.05) (Figures 3(a) and 3(b)). No significant differences were found between control and intervention groups (*p* = 0.74) or between boys and girls (*p* = 0.73). We did find a significant, inverse correlation between the amount of moderate/vigorous physical activity during school days and the BMI of the subjects (*r* = −0.26; *p* = 0.02).

FIGURE 2Average moderate/vigorous activity time in minutes per day. (a) During school and nonschool days and (b) during school day mornings and afternoons.

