Physical activity was objectively assessed in a random sample of 74 participants using the GENEActiv accelerometer (Activinsights Ltd., Kimbolton, United Kingdom). The participants were instructed to wear the accelerometer on their dominant wrist for 8 consecutive days and nights, including both weekdays and weekend days. Data were processed using RStudio software version 2022.07.2 + 576 (RStudio Team [2022]). RStudio: Integrated Development Environment for R. Boston, MA: RStudio, PBC) and the accelerometer manufacturer provided the processing algorithm for data segmentation and classification. The GENEActiv accelerometer is a triaxial accelerometer that measures acceleration in three orthogonal planes (*x*, *y*, *z*), which was configured at a sampling rate of 100 Hz. From the raw acceleration data, the processing algorithm provides activity intensity metrics, including time spent in sedentary, light, moderate, and vigorous physical activity. Classification is based on the vector magnitude of the acceleration signals. Specifically, the software calculates the Euclidean norm minus one (ENMO) of the acceleration signals, which provides a measure of the dynamic acceleration. For this study, only data relating to moderate and vigorous physical activity were considered. The number of participants was chosen based on the number of available accelerometers and available time for its use. We chose participants aged 8–9 years, in order to facilitate comparison with the PASOS 2019 study [26], the largest national study performed to date in Spain looking at the physical activity of children. We randomized the number of participants based on the type of school and arm (intervention vs control), aiming for a 1:1 ratio: 38 participants came from public schools and 36 from private and partially subsidized centers. A total of 37 participated in the intervention arm and 37 in the control arm.

Accelerometry data were analyzed separately for school days and nonschool days. For school days, we further stratified the analysis into two time periods: school hours (08:30 to 16:00) and after‐school hours (16:01 to 21:00), to distinguish between physical activity performed during school time and outside school hours. Minimum use included full use of the accelerometer during the study period (24 h/d for 8 days).

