### 2.5. Statistical Analysis

Sample size (286 kids in each arm of the study) was estimated using the “two independent means” approach, assuming an effect size of 0.75 BMI units (SD = 1.5), 80% power, *α* = 0.05 (two‐tailed), and an expected attrition rate of 15%. The effect size of 0.75 BMI units was selected based on a balance between clinical relevance and the practical limitations of our study. Given that our sample was limited to children who volunteered to participate, a larger sample was not feasible. Therefore, we opted for an effect size of 0.75 BMI units, which we considered both clinically meaningful in the context of pediatric obesity prevention [22, 24] and achievable within the constraints of our available sample size. Statistical analyses were performed using STATA version 14MP (StataCorp LLC, College Station, TX, USA).

Although the sample size calculation was initially performed at the individual level using a two independent means approach, we acknowledge that the cluster‐randomized design requires consideration of intracluster correlation (ICC). The absence of this adjustment may have led to an overestimation of statistical power, and this is recognized as a limitation. To appropriately account for clustering, all outcome analyses will be conducted using statistical models that consider the hierarchical structure of the data, with children nested within schools. Specifically, mixed‐effects regression models (or cluster‐robust standard errors) will be used to adjust for school‐level clustering.

In the descriptive statistical study, means, minimum and maximum values, and SD were calculated for quantitative variables. For qualitative variables, counts and proportions are presented. The 95% confidence interval for mean values and proportions was calculated. The hypothesis test for comparing proportions was used to verify the difference between proportions and the Student’s *t*‐test or Mann–Whitney test (if the distribution was not normal) was used to analyze differences between means of two samples. In the case of more than two samples, the tests applied were ANOVA or Kruskal–Wallis (non‐normal samples). Significant differences were considered when *p* < 0.05. Pearson correlation coefficient was used to evaluate the existence of correlation between average moderate/vigorous physical activity per day and BMI. Outcome assessors were blinded to school allocations to ensure unbiased evaluation of results.

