### 3.1. Anthropometry

Table 2 shows the characteristics of the participants.

**TABLE 2 tbl-0002:** Anthropometric characteristics in the pre‐intervention situation.

	Control (*N* = 259)			Intervention (*N* = 298)			*p*‐values
	*N*	Mean (%)	SD	*N*	Mean (%)	SD	
School type	8			5			
Public	87	33.6%	n/a	121	40.6%	n/a	0.063
Partially subsidized	120	46.3%	n/a	109	36.6%	n/a	
Private	52	20.1%	n/a	68	22.8%	n/a	
Sex^∗^ (girls)	155	59.8%	n/a	152	51%	n/a	0.036^∗^
Age^∗^ (years)		8.1	1.3		7.6	1.2	0.000^∗^
Height^∗^ (cm)		133.2	9.8		130.7	8.5	0.002^∗^
Weight (kg)		31.8	9.7		30.6	8.5	0.125
Body mass index (kg/m^2^)		17.6	3.4		17.6	3.2	0.957
Weight *z*‐score							
Normal (0)	170	65.6%	n/a	176	59.1%	n/a	0.245
Overweight (+1)	47	18.2%	n/a	60	20.1%	n/a	
Obesity (+2)	42	16.2%	n/a	62	20.8	n/a	
Triponderal body index		13.2 kg/m^3^	2.2		13.5 kg/m^3^	2.1	0.129
% of body fat		21.8%	7.1		22.8%	6.8	0.092
Waist circumference (cm)		61.4 cm	10.1		59.9 cm	9.5	0.050^†^

Abbreviation: SD, standard deviation.

^†^Kruskal–Wallis.

^∗^
*p*‐value < 0.05.

Both groups are comparable in weight, BMI, TMI, weight z‐score, and body fat percentage, with slight differences in age, sex distribution, and height.

The overall rate of overweight and obesity in our sample was 37.9%. When assessing the distribution of overweight and obesity among the different schools (public, subsidized, and private), we found a significantly higher proportion of overweight and obesity in public schools than in subsidized schools and a higher proportion in subsidized schools than in private schools (*p* = 0.001, Table 3).

**TABLE 3 tbl-0003:** Percentage of overweight and obesity by type of school.

	Type of school			
	Public	Partially subsidized	Private	Total
Adequate BMI, *N* (%)	107 (51.4)	153 (66.8)	86 (71.7)	346 (62.1)
Overweight, *N* (%)	46 (22.1)	41 (17.9)	20 (16.7)	107 (19.2)
Obesity, *N* (%)	55 (26.4)	35 (15.3)	14 (11.7)	104 (18.7)
Overweight + obesity (%)	48.6%	33.2%	28.3%	37.9%
Total (N)	208	229	120	557

*Note:* Pearson chi‐square: *x*
^2^(4) = 19.1993; *p* = 0.001.

Abbreviation: BMI, body mass index.

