### 4.2. Physical Activity

Regarding physical activity in our population, it is worth mentioning that we found significant disparities between the physical activity performed during school mornings and afternoons among centers, with more hours of moderate/vigorous physical activity in private and partially subsidized centers compared to public schools. Morning differences are explained by increased physical activity during school hours (increased recess or directed physical education/activities). Afternoon differences might be explained by more after‐school programs in private and partially subsidized centers or by SES differences playing a role in the decision to enroll the participating children in after‐school activities. This difference could partially explain the different prevalence of overweight and obesity between centers.

It is noteworthy that the average amount of physical activity observed in our study, at 4.2 h per day, substantially exceeds the WHO’s recommendation of 60 min daily. Our results differ from those reported in the PASOS 2019 study by Gómez et al. [26], which utilized the ActiGraph wGT3X‐BT accelerometer (Pensacola, FL, USA) in a broader Spanish population. They reported approximately 2.5 h as the mean time spent on moderate/vigorous physical activity for children aged 8–9 years. The 68% higher activity levels in our study warrant careful consideration.

Several factors may contribute to this discrepancy:

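### The activity–BMI correlation in section 3.3 is pooled and unadjusted, so it may partly reflect school type, and its significance is fragile

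*Protocol article*

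**What the plan says.** - **Method (section 2.5).** "Pearson correlation coefficient was used to evaluate the existence of correlation between average moderate/vigorous physical activity per day and BMI". No adjustment or stratification is attached to this test. Adjustment for school type is promised only for the multivariate analyses.
- **Sample (section 2.4).** "Physical activity was objectively assessed in a random sample of 74 participants using the GENEActiv accelerometer". Selection was by school type and arm, among children aged 8–9: "38 participants came from public schools and 36 from private and partially subsidized centers".
- **Result (section 3.3).** "We did find a significant, inverse correlation between the amount of moderate/vigorous physical activity during school days and the BMI of the subjects", with r = −0.26 and p = 0.02. The reported quantity is school-day activity, whereas section 2.5 names average activity per day.
- **Activity by school type (section 3.3).** "We found statistically significant differences in moderate/vigorous activity during the school day mornings and afternoons among center types" (p < 0.05). Section 4.2 gives the direction: public schools had less.
- **Weight status by school type (Table 3, all 557 children).** Overweight plus obesity was 48.6% in public, 33.2% in partially subsidized and 28.3% in private schools.

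**The concern.** If one group of schools has both lower activity and higher BMI, pooling the groups produces a negative correlation even when activity and BMI are unrelated inside each group. The article documents both gradients, and they run in that direction. School type was also a selection variable for the accelerometer sample, and section 2.5 elsewhere treats it as a covariate because of its known association with obesity. The correlation is nevertheless reported with neither adjustment nor caveat.

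At stake is how the sentence in 3.3 is read. It is the article's only direct estimate linking activity, which the programme targets, to BMI, whose change is the primary outcome. A reader will take it as an association between individual children's activity and their BMI. Part of it may be a difference between types of school.

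**Working it through.** **1. Reproduce the reported result.** Inputs: r = −0.26 (section 3.3), n = 74 (section 2.4).

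t = r·√(n−2)/√(1−r²) = −0.26·√72/√(1−0.0676) = −2.28, two-sided p = 0.025. The Fisher 95% CI is −0.46 to −0.03. Rounding of r (−0.255 to −0.265) gives p from 0.028 to 0.023, so the printed 0.02 is compatible. The result is correctly computed as an unadjusted test, and its interval already ends close to zero.

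**2. Link between school type and BMI (assumed).** The article gives no mean BMI by school type, so the weight categories in Table 3 are used.

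- Public: (46+55)/208 = 48.6% overweight or obese. Other types: (41+35+20+14)/349 = 31.5%.
- As a shift on a normal scale: z(0.486) − z(0.315) = −0.036 + 0.481 = 0.445 SD.
- As a correlation at the 38:36 split (q = 38/74): b = d/√(d² + 1/[q(1−q)]) = 0.445/√(0.198 + 4.003) = 0.217.
- Smaller gaps of 0.30 and 0.20 SD give b = 0.148 and 0.099.

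**3. Link between school type and activity (assumed).** Only p < 0.05 is reported. The smallest correlation that reaches p = 0.05 with n = 74 is:

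- public v other: a = t/√(t²+72) with t = 1.993, so a = 0.229;
- three types: a = √(2F/(2F+71)) with F = 3.126, so a = 0.284.

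If that p were as small as 0.001, a would be 0.375 (two groups) or 0.421 (three groups).

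**4. Correlation adjusted for school type.** Partial r = (r + a·b)/√[(1−a²)(1−b²)], with a and b as absolute values. The plus sign applies because the two gradients run in opposite directions. The share due to school type is a·b/0.26.

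| Assumed type–activity (a) | Assumed type–BMI (b) | Share of r | Adjusted r | p |
|---|---|---|---|---|
| 0.229 | 0.099 | 9% | −0.245 | 0.037 |
| 0.229 | 0.217 | 19% | −0.221 | 0.060 |
| 0.284 | 0.217 | 24% | −0.212 | 0.074 |
| 0.421 | 0.217 | 35% | −0.190 | 0.109 |

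(71 df for the two-group rows, 70 for the three-group rows.)

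Second row in full: (−0.26 + 0.0497)/0.950 = −0.221, t = −1.91, p = 0.060.

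**5. Wider range.** The school-type tests were on mornings and afternoons, not on the school-day amount that was correlated, so a could also lie below the minimum in step 3. The corners, at 71 df, are:

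- a = 0.15, b = 0.10: (−0.26 + 0.015)/0.984 = −0.249, p = 0.034 (share 6%);
- a = 0.50, b = 0.22: (−0.26 + 0.11)/0.845 = −0.178, p = 0.13 (share 42%).

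**6. Does the school-type mix of the 74 matter?** Public pupils are 38/74 = 51.4% of the accelerometer sample and 208/557 = 37.3% of the cohort. With the same within-type association and the same gaps between types, a 37.3% public share would give a pooled r of about −0.257 to −0.258 instead of −0.26. The mix is immaterial; what matters is pooling without adjustment.

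**The case against.** The strongest reply is that nothing stated is false. The article says a Pearson test was used to look for a correlation, and the value reproduces and meets the stated threshold. An adjusted association is a different quantity. The coefficient does not appear in the abstract or the closing conclusion, and the intervention effect will come from models that adjust for school type. All of that stands. It limits the point to how a secondary baseline result is reported and interpreted.

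It is also true that the size of the confounding is assumed. Table 3 covers weight categories in 557 children aged 6–10, not BMI in the 74 aged 8–9. Placing a three-group measure in a two-group formula is approximate, although the two-group minimum gives a similar answer (−0.22, p = 0.060). Every adjusted value lies well inside the unadjusted interval.

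Three stronger readings are tempting, and the documents do not support them.

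- **That the larger public-school share in the 74 drives the result.** It was a disclosed design choice and moves r by about 0.003 at most (step 6).
- **That section 4.2 argues in a circle.** It says "This difference could partially explain the different prevalence of overweight and obesity between centers", but the difference meant there is the activity gap between school types, not the correlation. Section 4.2 does not cite r, and the sentence is hedged.
- **That the word significant, or that sentence, should be deleted if the adjusted interval includes zero.** The unadjusted test is correctly reported, and an interval from 74 children that includes zero does not show absence of an association.

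What survives the reply is that the article identifies school type as a confounder, shows it related to both variables, and then leaves it out of this one association without saying so.

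**Conclusion.** The point holds as a reporting and analysis weakness of limited reach. The pooled r of −0.26 may partly reflect school type. In the main scenarios school type accounts for roughly 10–35% of it, and for less than half even at the extreme corner. The adjusted r is then about −0.25 to −0.18, with p about 0.03 to 0.13. Most of the association probably remains, but whether it falls below 0.05 after adjustment cannot be known from the article.

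These figures rest on three assumptions: the 74 children show a BMI gradient by school type no larger than the one implied by Table 3; the type–activity correlation lies between 0.15 and 0.50; and all 74 children contribute to r. Clustering of children within schools is not included because no intracluster correlation is given.

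**What to change.** Re-run the accelerometer records with the activity–BMI association adjusted for school type, either as a partial correlation or as a regression of BMI on activity with school type as a covariate. In section 3.3, report the adjusted estimate and its 95% CI beside the pooled r, and label the pooled r as unadjusted. Base any statement about a link between activity and BMI on the adjusted estimate.

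The cost is one re-analysis of data already collected and a sentence or two of text. The likely downside is a slightly weaker estimate that may no longer reach p < 0.05. No change to the sampling, to the activity means or to the planned intervention-effect models is needed.

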**Figure figpt-0003:**
[figure not shown]
(a)

**Figure figpt-0004:**
[figure not shown]
(b)

FIGURE 3Average moderate/vigorous activity time in minutes per day during school day mornings and afternoons. (a) Average moderate/vigorous activity time in minutes per day during school day and (b) average moderate/vigorous activity time in minutes per day during school day afternoons. Box plot and statistical analysis (*p*‐value). Center type: 1 (public); 2 (partially subsidized); and 3 (private).

**Figure figpt-0005:**
[figure not shown]
(a)

**Figure figpt-0006:**
[figure not shown]
(b)

## 4. Discussion

This study describes the design of a randomized, controlled, parallel clinical trial assessing the impact of an educational intervention on the prevalence of obesity in children, as well as the baseline description of the study population. School type was used as a proxy for SES. Socioeconomic disparities were clearly present in our measurements, with a wide gap in overweight and obesity rates between public (48.6%) and private schools (28.3%). Also, our study highlights the early onset of dysglycemia and dyslipidemia in our population, emphasizing the need for targeted programs for at risk population.

Some of the strengths of our project include the development of the program in collaboration with educational specialists, the inclusion of components related to nutrition, physical education, sleep, and overall health, as well as the presence of both school‐ and home‐based areas of intervention, all of which follow current recommendations emphasizing the need for multilevel strategies. Also, our program has been designed to be implemented at no cost for the school system (all the cost for the development of the program has already been paid for). It is scalable, low‐cost, teacher‐led, and a digital‐analog hybrid. The lack of significant baseline differences in weight, BMI, and body fat percentage between intervention and control groups supports the comparability of both arms, reinforcing the internal validity of the subsequent evaluation.

International organizations like the WHO or the American Heart Association recommend promoting cardiovascular health in children by maintaining adequate BMI, optimal physical activity, and a balanced diet [29]. Current evidence supports that the ideal components for an obesity intervention program should include at least a combination of nutritional and physical education components [8, 30], even though sometimes the effects are small [31]. Other lifestyle factors like sleep or television time have also been shown to be related to an increased risk of overweight and obesity [32]. The earlier age groups (5–11 years) provide a clear window of opportunity, since the effect of these interventions is likely smaller as they progress into adolescence [33]. Interventions in school have proven effective [9], even with simple measures as targeting the promotion of drinking water vs other sources of sugar‐rich drinks [34] or increasing physical activity [35] (even with small increases like 20 min/day [36]).

### 4.1. Obesity Prevalence and Disparities Among Schools

With regard to the evolution of overweight and obesity in Spain in the last decade, data from the COSI initiative (ALADINO in Spain) show an increase between 2011 and 2015–17, with subsequent stabilization. The PASOS study [26], conducted in 2019–2020, assessed the nutritional status of Spanish children aged 8–16 years. The results showed that 23.3% were overweight and 17.3% were obese [37], further supporting the decreasing trend observed in ALADINO. However, other studies suggest an ongoing increasing trend [38]. In any case, obesity rates remain high in our country and remain a primary area for intervention in child´s health. At 37.9%, our rate is slightly lower than those described by PASOS and ALADINO, but that is probably due to the overrepresentation of private schools in our sample.

Our findings reveal significant disparities in overweight and obesity rates among different school types, with public schools showing the highest prevalence (48.6%) compared to partially subsidized (33.2%) and private schools (28.3%). This socioeconomic gradient in obesity is consistent with previous studies in Spain and other developed countries [11, 12, 39]. The SES was a clear factor influencing overweight and obesity rates. These disparities were also present in the PASOS study, with the influence of parental education and income in overweight and obesity rates, with reported increased rates in lower SES [11]. Also, further highlighting the uneven distribution of overweight and obesity among different SES strata, the PASOS study showed that the stabilization of overweight and obesity rates described in the last years by ALADINO is at the expense of the higher socioeconomic levels.

Importantly, our results also highlight the early onset of metabolic complications in this population. We detected cases of elevated fasting blood glucose (21 cases) and hypercholesterolemia (24 cases) across both groups. Childhood obesity is associated with increased risk of type 2 diabetes, dyslipidemia, hypertension, and metabolic syndrome [2]. Longitudinal studies have found childhood obesity and cardiovascular risk factors track into adulthood, with obese children having a higher risk of becoming obese adults [40].

